### Statistics

All data will be analyzed using SPSS for Windows 17.0 Software (SPSS Inc., Chicago, IL, USA). For the main analysis, we will perform both an intent-to-treat principle and a per-protocol analysis. Measurement data will be described with mean ± standard deviation ($$ \overline{x} $$ ± SD), and count data will be expressed with number of cases and percentages. All statistical analyses will use two-tailed tests, and the level of significance will be set at *p* < 0.05 Additional file 2. 

Demographic and baseline characteristics of study participants by randomization group will be analyzed by an independent sample *t* test, *t*' test, or nonparametric test. In the comparison between the *De Qi* and control groups, the primary outcome (VAS scores) and secondary outcome (KOOS, in the form of symptom scores) will adopt the method of within-subject 6 × 2 factorial repeated measures analysis of variance (ANOVA) to analyze the integral analgesic effect, where the factors are time (six levels: baseline, and at the end of the 1^st^, 3^rd^, 6^th^, 9^th^, and 12^th^ treatments) and group (two levels: *De Qi* group and the control group). The immediate analgesic effect will be evaluated by the VAS score after the first treatment; the accumulated analgesic effect will be rated by the VAS score after the last treatment. They will be analyzed by the independent sample *t* test and *t*' test or nonparametric test. In addition, the overall *De Qi* scores of each group, i.e., the sum of the scores of all sensations in each treatment, will be considered and analyzed with the primary outcome by a bivariate correlation test (described by *r* and *p*).

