### Sample size

Patients with KOA will be randomized into two groups in a 1:1 ratio. The sample size for each group was calculated according to the following equation for a design with repeated measures [20] Additional file 2:$$ \mathrm{n}=\frac{2\kern0.5em *\kern0.5em {\upsigma}^2\kern0.5em {\left({\mathrm{u}}_{\alpha}\kern0.5em +\kern0.5em {\mathrm{u}}_{\upbeta}\right)}^2}{\updelta^2}\left\{\left[\frac{1}{\mathrm{r}}+\left(1-\frac{1}{\mathrm{r}}\right)\uprho \right]-\frac{\uprho^2}{1/ P+\left(1-1/ P\right)\rho}\right\} $$

where *P* stands for the number of observations prior to acupuncture (VAS score before the first intervention, one time point before treatment), and *r* is the observation number after acupuncture (VAS scores at the end of the 1^st^, 3^rd^, 6^th^, 9^th^, and 12^th^ treatments, a total of five time points after treatment). The values of ρ, α, μ_α_, and μ_β_ used here are as follows: ρ = 0.70 (usually between 0.50 and 0.75); α = 0.05 (bilateral); μ_α_ = 1.96; μ_β_ = 0.8417. As a result, an estimated sample size of 37 patients per group was obtained, assuming that a minimal difference of δ = 10 mm is considered as a clinically significant relief of chronic pain, as recommended by IMMPACT [21], and with a standard deviation (σ) of 29.5 mm of the VAS score for knee pain in all patients prior to treatment, according to the data from the clinical trial run by White et al. [22]. Considering a possible loss to follow-up of 20% Additional file 2, we planned to include total of 88 patients in our study.

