#### Knee pain intensity

To evaluate the efficacy of acupuncture treatment for KOA, knee pain intensity is measured via a 0–100 mm visual analog scale (VAS). The patient moves the slider on a 100-mm VAS ruler to indicate the intensity of knee pain that he/she is suffering, where the left end of the ruler marks “no pain,” and the right end marks “intolerable pain.” The distance (in millimeters) from the slider to the left end of the ruler is read directly from the back of the ruler by the researcher and is used as the VAS score for pain intensity, which is the primary outcome index in this study. The VAS score for knee pain intensity will be measured before each treatment and at the end of the 1^st^, 3^rd^, 6^th^, 9^th^, and 12^th^ treatments, as well as at the end of the follow-up visit (Fig. 3). Additional file 2

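### The primary VAS outcome has several unadjusted 0.05 tests in two main analysis populations and no named deciding test, although the trial was sized for one comparison

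*Protocol article*

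**What the plan says.** All references are to the protocol article.

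- **Outcome.** Under Knee pain intensity, the VAS score is the measure "which is the primary outcome index in this study". It is recorded before every treatment, after sessions 1, 3, 6, 9 and 12, and at the end of follow-up. No time point or contrast is singled out.
- **Tests.** Under Statistics, the VAS is analysed by a 6 × 2 repeated measures ANOVA (baseline plus five post-treatment visits, by group) for an overall effect. Separate two-group tests follow: after session 1 for the immediate effect, and after the last session for the accumulated effect.
- **Populations.** "For the main analysis, we will perform both an intent-to-treat principle and a per-protocol analysis".
- **Error level.** "All statistical analyses will use two-tailed tests, and the level of significance will be set at" 0.05. No order of testing and no adjustment is given.
- **Sample size.** One comparison is powered, with "α = 0.05 (bilateral"), "μ_β_ = 0.8417", "a minimal difference of δ = 10 mm", a "standard deviation (σ) of 29.5 mm of the VAS score for knee pain" and "ρ = 0.70 (usually between 0.50 and 0.75"). There is one baseline observation and five post-treatment observations. The result is 37 per group, raised to 88 in total.

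**The concern.** The Abstract and Discussion present the immediate and accumulated effects as joint aims, and the ANOVA adds an overall effect. Each is therefore a possible route to a positive conclusion about De Qi, and each can be followed in two populations. If the results disagree, the text gives no rule for which one stands. The 5% error rate assumed in the sample size then no longer describes the chance of a false positive claim.

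The role of the per-protocol analysis matters in its own right. It removes patients after randomization and so loses the protection of randomization. In a superiority comparison it should not be able to carry the conclusion when ITT does not.

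There is also a mismatch. None of the tests in the Statistics section is the comparison for which the trial was sized.

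**Working it through.** **1. Reproduce the sample size.** Inputs from the Sample size section: σ = 29.5, δ = 10, ρ = 0.70, P = 1, r = 5, u values 1.96 and 0.8417.

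n = [2σ²(u_α + u_β)²/δ²] × {[1/r + (1 − 1/r)ρ] − ρ²/[1/P + (1 − 1/P)ρ]}

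- Bracket: (0.2 + 0.8 × 0.70) − 0.49/1 = 0.76 − 0.49 = 0.27
- Leading term: 2 × 870.25 × 2.8017²/100 = 136.6
- n = 136.6 × 0.27 = 36.9, so 37 per group, as stated.

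The factor 0.27 is the variance, relative to σ², of the mean of five post-treatment scores after adjustment for one baseline score. That is the single comparison the trial was sized for.

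**2. Compare with the tests actually planned** (37 per group, normal approximation, a constant 10 mm difference at the five post-treatment visits and none at baseline).

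- Baseline-adjusted post-treatment mean: 80% power, by construction.
- Unadjusted test at one visit: SE = 29.5 × √(2/37) = 6.86; 10/6.86 − 1.96 = −0.50; power about 31%.
- ANOVA group effect with baseline as a time level: the difference in the six-visit mean is 10 × 5/6 = 8.33; its variance factor is 1/6 + (5/6) × 0.70 = 0.75; SE = 29.5 × √0.75 × √(2/37) = 5.94; 8.33/5.94 − 1.96 = −0.56; power about 29%.

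**3. False-positive rate under no effect.** Trials were simulated with 44 per arm (88/2), six visits, normal data, equal correlation ρ = 0.70 and each test at two-sided 0.05. The interaction test was Greenhouse-Geisser corrected in the main runs. The per-protocol set was a random 80% of patients. Ranges are across independent runs.

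| What counts as success | False-positive rate |
|---|---|
| ANOVA group effect, ITT only | about 5% |
| ANOVA group effect, ITT or per-protocol | about 7% |
| Immediate or accumulated, ITT | 7.8–8.7% |
| The same plus ANOVA group effect, ITT | 8.9–9.9% |
| The same plus group × time, ITT | 12.7–14.0% |
| Group effect, immediate or accumulated, in either population | 12.7–13.0% |
| All four tests, in either population | 17.9–19.3% |
| Group effect, immediate or accumulated, each required in both populations | 5.5–5.9% |

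Most runs had 20,000 trials. Near 13% the simulation standard error is √(0.13 × 0.87/20,000) = 0.24 percentage points, so differences of a few tenths between runs mean nothing.

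**4. Sensitivity.** With ρ from 0.50 to 0.75, or a first-order autoregressive structure with parameter 0.8 or 0.9, the four tests give 12.7–14.2% in ITT and 17.7–19.5% when either population counts. For comparison, four independent tests would give 1 − 0.95⁴ = 18.5%.

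**The case against.** A reader might infer that nothing in the protocol points to a deciding analysis. That goes too far. The Statistics section attaches the words primary outcome to the repeated measures ANOVA, and the Sample size section uses a repeated measures formula with one α. Together they suggest that a repeated measures comparison is the intended primary analysis. What stands is that this is only implied, and that the ANOVA as specified is not the quantity the formula powers.

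A reader might also state flatly that the false-positive rate is 13–19%. The protocol does not support that. The figure needs any single significant result to count, and in addition either the interaction to count as a separate success or a win in one population to be enough. The protocol states none of these rules and never names an interaction test, although a factorial ANOVA normally yields one. Nor does it say that per-protocol may override ITT. Performing both analyses may mean checking that they agree, and in that case the second population adds no inflation.

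The immediate and accumulated effects are two prespecified aims with one defined time point each, not a search over sessions. Whether separately reported questions must share one α is partly a matter of judgement. For that reason, making both aims wait on a significant overall test would be debatable.

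Finally, a testing order is often left to an analysis plan, and none is shown. That would answer silence, but the article is not silent. It gives both populations main-analysis status and sets one unadjusted level for every test.

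**Conclusion.** The point holds as a lack of a stated decision rule, combined with a mismatch between the powered comparison and the planned tests. At ρ = 0.70, if any one significant result is claimed, the false-positive rate is about 8–10% in ITT for the immediate and accumulated tests with or without the ANOVA group effect. It is about 13–14% if group × time also counts, and about 13–19% if either population suffices, the lower end without the interaction and the upper end with it. If the group effect and the two session tests count only when both populations agree, it is about 5–6%; counting the interaction as well would raise that.

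The rate is therefore set by a rule the protocol does not give. The figures assume normal data, equal correlation between visits and a per-protocol set that is a random 80% of patients, none of which can be checked from the document. They leave out the KOOS, the De Qi correlation and the open choice between t, t′ and nonparametric tests. The trial data remain usable; what is at risk is a headline claim presented at a nominal 5%.

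**What to change.** - Name one primary test: the ITT group difference in mean VAS over the five post-treatment sessions, adjusted for baseline, at two-sided 0.05. This is the comparison that the Sample size section powers at 80%.
- Make per-protocol a sensitivity analysis that cannot support a claim on its own.
- Report the immediate and accumulated contrasts as secondary aims, with Holm adjustment if either is to be claimed as confirmatory.
- Fix this before any analysis by group, including analysis under the A/B codes. Waiting until just before unblinding is not safe, because the Randomization and blinding section places unblinding after data analysis is complete. The Trial status section reports treatment and follow-up still under way, so at that date the change could still be made without sight of results by group.

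The cost is a short change to the text and a baseline-adjusted model for the primary test, with no new patients or data. The downside is that an isolated significant session, or a result seen only in the per-protocol set, can no longer be presented as the trial's primary result.

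### The sample size is for a baseline-adjusted mean of five post-treatment VAS scores, but the planned 6 × 2 ANOVA makes baseline an outcome level and names no deciding term, so the 80% design power is not assured

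*Protocol article*

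**What the plan says.** Protocol article, Sample size: "The sample size for each group was calculated according to the following equation for a design with repeated measures". The formula takes one observation before treatment (P = 1) and five after it (r = 5, at the end of sessions 1, 3, 6, 9 and 12). The correlation between measurements is entered as "ρ = 0.70 (usually between 0.50 and 0.75"). The significance level is entered as "α = 0.05 (bilateral"). Power enters only through "μ_β_ = 0.8417", which corresponds to 80% although the percentage is not written. The difference is set by "assuming that a minimal difference of δ = 10 mm is considered as a clinically significant relief of chronic pain". The spread comes from an earlier acupuncture trial and is described in the words "with a standard deviation (σ) of 29.5 mm of the VAS score for knee pain in all patients prior to treatment". The result is 37 per group, and 88 in total after an allowance for 20% loss to follow-up.

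Protocol article, Statistics: VAS and KOOS are to be compared between groups by a "within-subject 6 × 2 factorial repeated measures analysis of variance (ANOVA) to analyze the integral analgesic effect". Group has two levels. That baseline is itself a level of the outcome is explicit, since the layout opens with "where the factors are time (six levels: baseline, and at the end of the" and goes on to list the five post-treatment assessments. The immediate effect (VAS after session 1) and the accumulated effect (VAS after session 12) are compared by separate two-sample t, t' or nonparametric tests. No baseline covariate is mentioned for any of these comparisons, and no term of the ANOVA is named as the deciding test.

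**The concern.** The two sections use the baseline score in different ways. In the sample-size formula it is a predictor that removes variance from the post-treatment mean. In the ANOVA it is one of the outcomes. Under randomisation the expected group difference at baseline is zero, so the group main effect averages that zero in with the five post-treatment differences and gains no precision from baseline. The interaction does remove between-patient variance, but it is a 5-df test whose power depends on how the difference evolves over sessions, and the sample-size section says nothing about that.

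At stake is whether the trial has the power it was sized for. The Background describes the contribution of *De Qi* as controversial, so a non-significant result from an underpowered test could be read as evidence against it. Recruitment of all 88 participants is complete (Trial status), so the gap can no longer be closed by enrolling more patients.

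**Working it through.** **Inputs** (Sample size section): σ = 29.5 mm, δ = 10 mm, ρ = 0.70, u_α = 1.96, u_β = 0.8417, P = 1, r = 5. **Assumptions:** equal SD and equal correlation at all six times, which the formula implies; no difference at baseline; and, unless stated otherwise, 10 mm at each of the five post-treatment times. Power uses the normal approximation, except that the interaction uses the noncentral F distribution.

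**1. The plan's own figure.**
- Multiplier: 2 × 29.5² × (1.96 + 0.8417)² / 10² = 136.6.
- Bracket: [1/5 + (4/5) × 0.70] − 0.70² = 0.76 − 0.49 = 0.27.
- n = 136.6 × 0.27 = 36.9, so 37. The figure reproduces.

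The factor 0.27 is the variance of the mean of five post-treatment scores after regression on one baseline score, in units of σ². The power for that analysis is 80.1% at 37 per group and 86.4% at 44.

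**2. Group main effect of the 6 × 2 ANOVA.**
- Diluted difference: 10 × 5/6 = 8.33 mm.
- Variance factor of a six-score mean: 1/6 + (5/6) × 0.70 = 0.75, so SD = 29.5 × √0.75 = 25.55 mm.
- At 37 per group: SE = 25.55 × √(2/37) = 5.94, z = 8.33/5.94 = 1.40, power 28.9%. A simulation of 20,000 trials gave 28.3%.
- At 44 per group: 33.4%.
- For 80% power: 136.6 × 0.75/(5/6)² = 147.6, so 148 per group.

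**3. Group × time interaction (5 df).**
- Sum of squared deviations of the six differences (0, 10, 10, 10, 10, 10) about their mean: 83.33.
- Noncentrality at 37 per group: (37/2) × 83.33 / (29.5² × 0.30) = 5.91. With F(5, 360), power is 42.0% (41.8% simulated).
- At 44 per group: noncentrality 7.02, power 49.6%.

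**4. Unadjusted t test at session 1 or 12.** z = 10/(29.5 × √(2/37)) = 1.46, power 30.8%; 35.6% at 44 per group.

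**5. Other values of ρ.** Over the protocol's quoted range of 0.50 to 0.75, at 37 per group, the main effect runs from 35.6% down to 27.6% and the interaction from 25.6% up to 49.9%.

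**6. Other effect profiles** (illustrative, not from the protocol; ρ = 0.70):

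| Difference at sessions 1, 3, 6, 9, 12 (mm) | Mean (mm) | Interaction, 37 / 44 per group | Main effect, 37 per group |
|---|---|---|---|
| 10, 10, 10, 10, 10 | 10 | 42% / 50% | 29% |
| 5, 7.5, 10, 12.5, 15 | 10 | 69% / 77% | 29% |
| 4, 7, 10, 13, 16 | 10 | 77% / 85% | 29% |
| 2, 6, 10, 14, 18 | 10 | 91% / 95% | 29% |
| 2, 4, 6, 8, 10 | 6 | 35% / 42% | 13% |

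The main effect depends on the profile only through its mean; the interaction depends on its shape.

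**The case against.** The strongest reply is that the group main effect is not obviously the test that matters. With baseline as a time level, the interaction is the term that asks whether the groups diverge from a common start, and its error term uses σ²(1 − ρ), so it does remove between-patient variance. The protocol also sets out to separate immediate from accumulated effects, so a difference that grows over sessions is part of its own question. For growing profiles that average 10 mm the interaction can come close to 80% or exceed it.

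This stands, and it limits what can be claimed. A reader might infer that the planned analysis simply has 29% power. The document does not support that, because it does not choose the main effect. A reader might also infer that a true 10 mm effect would most probably be reported as non-significant. That does not follow either. Under the constant-effect assumptions the two ANOVA terms are independent, so the chance that at least one is significant is about 1 − (1 − 0.289) × (1 − 0.420) = 59% at 37 per group, and 1 − (1 − 0.334) × (1 − 0.496) = 66% at 44. Taking whichever term succeeds would raise a multiplicity problem, so this does not defend the plan.

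Finally, the within-subject label might suggest that group will be tested against the wrong error term. Group is plainly defined as the randomised two-level factor, so this is loose wording and no evidence of a wrong test.

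The reply does not remove the mismatch. The sample-size formula assumes a baseline adjustment that no planned comparison makes, and the deciding term is left open.

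**Conclusion.** The point holds as a mismatch between the sample-size calculation and the analysis. The 37 per group is correct for a baseline-adjusted mean of five post-treatment VAS scores. With a constant 10 mm difference, none of the planned VAS comparisons reaches the intended 80%: about 29% for the group main effect, 42% for the interaction and 31% for a single-session t test at 37 per group, or 33%, 50% and 36% if all 44 per group are analysed. The interaction does better if the difference grows and still averages 10 mm, and worse if 10 mm is reached only at session 12. The design power therefore rests on a choice of term and an effect profile that the protocol does not state.

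These figures assume equal SDs and equal correlations of 0.70. The tests remain valid under randomisation; the defect is lost efficiency and an unnamed deciding test, not bias.

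**What to change.** Before unblinding, replace the 6 × 2 ANOVA for VAS with a model of the five post-treatment scores (sessions 1, 3, 6, 9 and 12), with pre-treatment VAS as covariate and with group (between patients), session and group × session. Name the group difference averaged over the five sessions as the primary test of the integral effect, because that is what the 37 per group was computed for.

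Estimate the immediate (session 1) and accumulated (session 12) effects as baseline-adjusted contrasts from the same model, in place of the unadjusted t tests. This keeps the protocol's distinction between them. Adjustment lowers the single-session variance factor from 1 to 1 − 0.70² = 0.51, so z = 10/(29.5 × √0.51 × √(2/37)) = 2.04 and power for 10 mm rises from 31% to about 53%. These contrasts should therefore be reported as estimates with confidence intervals and not presented as powered at 80%.

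Using the same model for KOOS is optional and does not rest on the sample-size calculation, which concerns VAS only.

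The cost is one paragraph of analysis wording. It needs no new patients or measurements. Treatment and follow-up were still under way when the article was written, and the protocol defers unblinding until the analysis is complete, so the change can be made and dated without knowledge of the results by group.

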**Methods/design:**

Eighty-eight patients with KOA will be recruited and randomly assigned to the *De Qi* group (enhanced stimulation to evoke *De Qi*) and the control group (weak stimulation to avoid *De Qi*) in the Department of Acupuncture and Physical Therapy, Beijing Luhe Hospital Affiliated to Capital Medical University. Each patient will receive three 30-minute sessions per week for 4 consecutive weeks and undergo a 1 month follow-up. The severity of knee pain, as measured on a 100-mm visual analog scale (where 0 indicates no pain and 100 indicates intolerable pain) will be used as the primary outcome, and the Knee injury and Osteoarthritis Outcome Score will be used as the secondary outcome. Both indexes will be measured before and after the 1^st^ (for evaluating the immediate analgesic effects), 3^rd^, 6^th^, 9^th^, and 12^th^ (for evaluating the accumulated analgesic effects) treatments and at the end of the follow-up. The intensity of the *De Qi* sensation will be assessed by the Chinese-Modified Massachusetts General Hospital Acupuncture Sensation Scale at the end of each treatment. Side effects during the treatments will be recorded and analyzed as well. The comparisons between the *De Qi* group and the control group will be done by using both an intention-to-treat analysis and a per-protocol analysis.

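### Without imputation, the planned repeated-measures ANOVA and last-treatment t test turn the intention-to-treat analysis into an analysis of completers

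*Protocol article*

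**What the plan says.** The Statistics section of the protocol article applies to VAS (primary) and KOOS (secondary) a 6 × 2 "repeated measures analysis of variance (ANOVA) to analyze the integral analgesic effect". One factor is group. The other is "time (six levels: baseline, and at the end of the 1^st^, 3^rd^, 6^th^, 9^th^, and 12^th^ treatments". The immediate and accumulated effects are the VAS scores after the first and last treatments, compared between groups by a t test or a nonparametric test.

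On the analysis population, the same section says: "For the main analysis, we will perform both an intent-to-treat principle and a per-protocol analysis". The Abstract repeats that the group comparisons "will be done by using both an intention-to-treat analysis and a per-protocol analysis". On software: "All data will be analyzed using SPSS for Windows 17.0 Software".

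The Sample size section obtains 37 patients per group and raises the total to 88: "Considering a possible loss to follow-up of 20" per cent. The article names no imputation and no other means of keeping a patient with a missing score in the ANOVA.

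**The concern.** A classical repeated-measures ANOVA, as the SPSS repeated-measures procedure runs it, needs a complete row per patient. One missing score out of six removes the patient, including every score that was observed. The last-treatment t test needs one score, but it is the one that all early leavers lack. Run in this way, both analyses use only patients who stayed, whatever population label they carry.

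Two things are at stake. First, the intention-to-treat result would differ from the per-protocol result mainly by protocol deviators with complete data, so reporting both would reassure less than it appears to. Second, if patients with little relief leave one arm more often than the other, the comparison of those who remain is no longer protected by randomisation. Differential loss is possible in a 12-session course in which one arm receives shallow needling without manipulation, but nothing in the article shows that it will occur.

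**Working it through.** **Inputs.** From Sample size: σ = 29.5 mm, δ = 10 mm, ρ = 0.70, P = 1, r = 5, "α = 0.05 (bilateral") with u_α = 1.96, "μ_β_ = 0.8417", 37 per group, 88 in total, 20% loss. From Statistics: six time levels, none of them the follow-up visit. Differences are De Qi minus control, so negative values favour De Qi.

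**1. The plan's own figure.** The bracket in the formula is [1/5 + (4/5)(0.70)] − 0.70² = 0.76 − 0.49 = 0.27. Then n = 2 × 29.5² × (1.96 + 0.8417)² / 10² × 0.27 = 36.89, so 37 per group. This reproduces.

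**2. Patients and power after listwise deletion.** 88 × 0.8 = 70.4, about 35 per group. The effective SD is 29.5 × √0.27 = 15.33 mm. Power ≈ Φ(10 / (15.33 × √(2/n)) − 1.96):

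| n per group | Power |
|---|---|
| 37 | 80.1% |
| 35 | 77.9% |
| 44 | 86.4% |

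An analysis that keeps partial data lies between 78% (partial data add nothing) and 86% (nothing lost).

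**3. Isolated missed visits.** If each of the five post-treatment scores is missing independently with probability 1%, 2%, 3% or 5% (assumption), the share of patients with all five is 0.99⁵ = 95%, 90%, 86% or 77%.

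**4. Bias, extreme case (assumption).** True difference −10 mm at every post-treatment visit; all pairs of visits correlated 0.70; the 20% of controls with the worst session-3 pain leave; De Qi loss is random.

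- Removing the top 20% of a normal variable lowers its mean by φ(0.8416)/0.8 = 0.350 SD, here 0.350 × 29.5 = 10.32 mm at session 3.
- Session 12 falls by 0.70 × 10.32 = 7.23 mm, so the completer difference is −10 + 7.23 = −2.8 mm.
- If leaving depends on session-3 pain plus independent noise of SD 29.5, the shift is divided by √2: 7.23/√2 = 5.11, giving −4.9 mm.
- Simulation of the same two cases gave −2.73 and −4.95 mm for completers. An estimator using the visits before dropout gave −9.95 and −9.97 mm.

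**5. Which analysis carries the bias.** In the same extreme case:

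| Quantity among completers | Pure ranking | With noise |
|---|---|---|
| Session-12 level (t test) | −2.8 | −4.9 |
| Mean of five post-treatment levels (drives the group main effect) | −10 + 0.76 × 10.32 = −2.2 | −10 + 7.84/√2 = −4.5 |
| Session 12 minus baseline | −10.0 | −10.0 |
| Mean post minus baseline | −10 + (0.76 − 0.70) × 10.32 = −9.4 | −10 + 0.62/√2 = −9.6 |

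Change from baseline survives because selection on session 3 lowers the retained controls' baseline by the same 7.23 mm as their session-12 score. Across the scenarios simulated, change contrasts stayed at about −9.3 to −10.1 mm.

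**6. Other loss patterns (assumptions), session-12 completer difference.**

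| Pattern | Result |
|---|---|
| Random loss in both arms | −10 |
| Worst-pain 20% lost in each arm | −10 |
| One common pain threshold, 20% lost overall | −7.1 (ranking), −8.5 (noise) |
| Worst-pain loss, 30% control and 10% De Qi | −3.8 (ranking), −5.6 (noise) |

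**The case against.** The strongest reply is that the conflict rests on silence. Imputing first and then running the ANOVA would satisfy both statements, and a condensed article may leave imputation to a fuller document. That stands as a limit: a reader might infer that the plan has no means of handling missing scores, and the article does not support that. What remains is narrower. The article names a method, fixes its six levels and attaches an intention-to-treat label, and the method as named does not deliver the label. An unseen document would have to add to the stated method to repair it.

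A reader might also infer that the ANOVA as a whole shrinks a 10 mm effect to about 3 mm. It does not. That figure belongs to the session-12 t test, with similar attenuation in the group main effect. Baseline is a level of the time factor, so the time-by-group contrast compares changes within the same patients and is nearly unbiased in the scenarios examined. This protection depends on the assumed equal correlation between visits.

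The one-sided scenario is deliberately extreme. Patients are to be blinded to allocation (Randomization and blinding), and the exclusion criteria remove those unable to complete the course. With equal pain-related loss in both arms, the session-12 bias vanishes.

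Two further inferences go too far. One is that 20% of patients will leave the ANOVA: the figure is a possible loss, and losses after session 12 remove nobody. The other is that the intention-to-treat and per-protocol sets would be identical: the article does not define the per-protocol set, and deviators with complete data would be in the former only.

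**Conclusion.** The point holds in a limited form. Unless missing scores are imputed first, the planned ANOVA and the last-treatment t test are completer analyses under an intention-to-treat label. At the ceiling of 20% loss before session 12, about 35 per group remain, with about 78% power against the planned 80%. That power cost is small.

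The more serious risk is selection bias, and it is conditional. It is essentially nil at session 12 under random or equally pain-related loss. It reaches about 5 to 7 mm of a true 10 mm in the t test under extreme loss related to pain in the control arm only, with the group main effect also attenuated and the time-by-group contrast nearly intact. The millimetre figures assume normal scores, σ = 29.5, ρ = 0.70 between all visits and dropout driven by session-3 pain. They illustrate what could happen and do not predict it. The point deserves correction because the accumulated effect is defined by the most exposed comparison.

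**What to change.** Analyse VAS and KOOS with a linear mixed model for repeated measures in the same software, using every observed visit of all randomised patients with at least one post-treatment score, and baseline as a covariate. Take the session-1 and session-12 group differences from that model in place of the separate t tests. Describe this set as an approximation to intention-to-treat, since patients with no post-treatment score are still left out, and report their number by arm.

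The model relies on dropout being explained by the scores observed before it, so add one sensitivity analysis that assigns unfavourable values to dropouts.

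The cost is revised analysis wording and a different procedure in the same package, with no new data or visits. Trial status reports treatment and follow-up still under way, and Randomization and blinding defers unblinding until the analysis is complete, so the change can be fixed before allocation is known.
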